## Abstract

**Objectives:**

Establishment of effective evidence-based interventions in rehabilitation of working memory (WM) deficits after acquired brain injury (ABI) is sorely needed. Despite robust evidence for the efficiency of clinical hypnosis in a wide range of clinical conditions, and improved understanding of mechanisms underlying its effects, the potential of clinical hypnosis in cognitive rehabilitation is underexplored. A recent study has shown large effects of hypnotic suggestion on WM capacity following ABI. This randomized controlled trial aims to evaluate and explore the replicability of these findings and examine the generalization of treatment effects. The study will also explore possible mechanisms of change.

**Methods:**

Ninety patients will be recruited from the Sunnaas Rehabilitation Hospital. Inclusion criteria are nonprogressive ABI, minimum 12-month post-injury, ongoing WM deficits, and age between 18 and 67 years. Patients will be randomized to either (a) an intervention group receiving four weekly 1-h sessions with induction and hypnosis, (b) an active control group receiving four weekly 1-h sessions of induction and mindfulness, or (c) a passive control group without intervention. The targeted procedure consists of suggestions about enhancing WM functions, for example through the instantiation of preinjury WM capacity in the present using age regression or through visualizations of brain plasticity. The non-targeted suggestions contain no explicit mention of ABI- or WM-related abilities. Each participant will be assessed at baseline, immediately after intervention, and 6 months after baseline. The primary outcome is the WM index from WAIS-IV and self- and informant-reported WM subscale from BRIEF-A, a questionnaire exploring executive functioning in everyday life. Secondary outcomes include a cognitive composite score derived from tests measuring processing speed, executive functions, learning capacity and memory, and self-reported measures of emotional distress, quality of life, and community integration. Exploratory measures include self-rated ABI and WM-related self-efficacy.

**Discussion:**

Rehabilitation of impaired WM after ABI has hitherto yielded limited transfer effects beyond the training material, i.e., improvement effects on everyday WM capacity, and clinical trials of new interventions are thus warranted. Long-standing empirical evidence demonstrates that hypnosis is an effective therapeutic technique in a wide range of conditions, and recent exploratory research has suggested a high efficacy of hypnosis in improving WM capacity in patients with ABI. However, these extraordinary findings need replication in studies applying scientifically rigorous designs. If successful, our ambition is to provide recommendations and materials to implement hypnotic suggestion as an adjunct treatment following ABI. Study findings may inform future studies exploring the use of clinical hypnosis in other areas of rehabilitation, such as mild TBI, and in other neurological conditions where WM deficit is prominent.

**Trial registration:**

ClinicalTrials.gov NCT05287542. Registered on March 2022

**Protocol version:**

Protocol version 2.0, December 2023.

**Supplementary Information:**

The online version contains supplementary material available at 10.1186/s13063-023-07867-z.

## Introduction

### Background

Working memory (WM) is regarded as the “sketchpad of conscious thought” [1], a cognitive capacity that holds and manipulates a limited amount of information for a short time in order to produce a response [2]. Multiple brain regions are involved in WM, and WM impairment is one of the most prevalent symptoms after acquired brain injury (ABI) [3], regardless of lesion etiology, localization, and severity [4]. WM is a central cognitive ability upon which rehabilitation for other functions depends and is a predictor for rehabilitation outcome, activity of daily living (ADL), physical rehabilitation, need for community services after discharge from hospital, community participation, and occupational status [5–10]. Rehabilitation efforts to improve high-level cognitive functioning following ABI have yielded limited clinically relevant effects so far [11–13]. Despite repeated administrations, reviews of biological interventions such as pharmaceuticals [14], noninvasive brain stimulation [15], physical exercise [16], and nutrition [17] show effect sizes in the zero to moderate range. Mindfulness can potentially reduce ABI-related fatigue. However, no significant effect on WM is found [18]. Treatment of WM through computerized training programs is widespread, regardless of systematic reviews reporting small to no clinically WM-relevant changes [19]. A comprehensive review of the brain-training literature reported no evidence for improvements on “far-transfer” cognitive abilities [19]. In other words, the improvements failed to generalize to other capacity-dependent activities [20]. Previous WM rehabilitation efforts have typically focused on “bottom-up” training programs that aim to restore function through repeated drills and graded exercise [12], where transfer of effects to untrained functional domains has not been documented.

In contrast to the train and drill bottom-up approach, the use of clinical hypnoses represents a “top-down” approach and has been suggested by Lindeløv and colleagues [4], to improve WM performance and to potentially enable generalization to other contexts.

The hypnotic state is a condition of openness to suggestions so that they may be used to elicit changes in a diverse array of psychological and bodily functions [21]. Reviews of hypnotic treatment in psychology [22] and medicine [23] are impressive, with demonstrated efficacy for anxiety [24], depression [25, 26], chronic pain [27], and headache [28] as an adjunct or alternative to anesthesia during surgery [29], in neurorehabilitation for motor disorders [30, 31], pain and vertigo [32], and aphasia [33]. Recent publications have made advancements in identifying the neural correlates underlying the hypnotic state [34]. Recently, hypnotic suggestions were found to enhance updating in WM in healthy adults, which was associated with changes in event-related potentials (ERP) in WM-related regions of the brain [35], indicating that hypnotic suggestions can be potent in altering cognitive functions*.* A few hypnosis studies have been conducted aiming at enhancing cognitive and psychological functions after ABI [36–38]. However, previous studies suffer from one or more major methodological weaknesses, such as a lack of control groups, lack of detailed descriptions of participants, randomization, blinding of testers, statistical procedures, and suggestions used during hypnosis.

The only randomized controlled trial (RCT) to date to include hypnosis in WM rehabilitation was performed by Lindeløv and colleagues [4]. This RCT included 68 participants with ABI across 3 treatment arms: an intervention group, an active control group, and a passive control group. The intervention included techniques such as age regression and visualizations of brain plasticity with suggestions about enhancing WM functions through the instantiation of preinjury WM ability in the present. The non-targeted suggestions contained no explicit mention of ABI or WM-related abilities but was otherwise matched in length and procedure, thus serving as an active control. Contrary to previous research, this study reported large effect sizes after only four 1-h sessions in favor of the intervention group compared to both active controls (Bayes factors of 342 and 37.5 on the two aggregate outcome measures) and the passive control group (Bayes factor = 1.7 × 10^13^). The long-term effect remained at approximately 6-week follow-up (Bayes factors = 7.1 and 1.3 in favor of no change). The outcome measures were neuropsychological tests, i.e., the WM index from WAIS-IV and Trail Making Test A and B. The authors suggest that hypnosis can improve WM following ABI, and that the speed and magnitude of the improvements indicate that there may be a potential for releasing residual cognitive capacity after ABI rather than “building” it anew. However, this study lacked medical data such as brain injury characteristics; it included only a few outcome measures (i.e., neuropsychological tests) and, most importantly, no measures of everyday WM capacity. Furthermore, Lindeløv and colleagues did not explore the potential underlying mechanisms associated with improved WM among the participants.

Self-efficacy theory asserts that an individual’s beliefs in personal competency predict actual performance [24], and ABI survivors often display negative self-expectancies and show lower WM self-efficacy than healthy controls [25]. Self-efficacy influences coping style and quality of life, satisfaction with functioning [26], social participation [27], functional independence [28], and community integration [29] after ABI. Thus, changed expectations about the possibility of dealing with the consequences of brain injury, i.e., improved self-efficacy, are a potential candidate in mediating generalization effects in cognitive rehabilitation [26]. Hypnosis seems to be particularly well positioned to enhance self-efficacy [30] and change expectations of psychological and behavioral outcomes in order to build confidence in one’s ability to cope with or solve problems [31, 32, 39, 40]. A person’s brain injury expectations may influence their cognitive performances through mechanisms similar to the nocebo effect [41]. Nocebo is a self-fulfilling prophecy where adverse effects are produced by expectations [42, 43]. The Cognitive Activation Theory of Stress (CATS) [44] suggests that expectancies regulate bodily stress responses [45]. This is relevant to the current study given the established negative influence of stress-related cortisol on WM capacity [46]. Specifically, expectations about coping (i.e., self-efficacy) may reduce the stress response, while expectations of helplessness or hopelessness may sustain it [44, 47]. This study will test the hypothesis that hypnosis in WM rehabilitation exerts its effect partly through changes in WM self-efficacy.

### Objectives and hypothesis

The main objective of this study is to explore the effect of hypnotic suggestion on WM capacity in adults with ABI. The following three research questions will be explored:

*Are the strong effect of hypnotic suggestion on WM performance in ABI patients found by Lindeløv et al. (2017) replicable?*

Our hypothesis is that the direction and the magnitude of the effects on WM found by Lindeløv and colleagues after four treatment sessions will be replicated. Given the large changes seen in Lindeløv et al.’s study, even weaker results are of clinical interest.

2.*Does hypnotic suggestions improve everyday WM, everyday functioning and participation, emotional status, and quality of life in ABI patients?*

The intervention is hypothesized to improve WM performance through “top-down” processes, which will allow improved WM capacity to be applied across diverse tasks and contexts. Thus, we expect to see treatment-related change in the domains of daily life, emotional status, and quality of life.

3.*Does increased self-efficacy predict the effect of hypnosis on WM?*

We hypothesize that changes in self-efficacy predict WM improvements following hypnosis.

## Methods

### Trial design

The study is organized as a randomized controlled superiority trial with parallel group design and three arms including (1) an intervention group, (2) an active control group, and (3) a passive control group. Participants will be randomly allocated in a 1:1:1 ratio to either of the three groups. The intervention group will receive four weekly 1-h sessions with hypnosis treatment (induction + hypnotic suggestion), while the active control group will receive four weekly 1-h sessions of non-targeted hypnotic suggestions (induction + mindfulness-based instructions) to factor out nonspecific treatment effects. The passive control group will be assessed at the same time points as the other two groups to isolate retest effects. Each participant will be assessed three times: (1) at baseline (T1), (2) immediately after the intervention which is 5 weeks post baseline (T2), and (3) 25 weeks after baseline (T3, follow-up). The study will follow the CONSORT statement facilitating complete and transparent reporting and aiding critical appraisal and interpretation (http://www.consort-statement.org/). This study expands the design of Lindeløv et al.’s study through a larger number of participants, the inclusion of far-transfer outcome measures, and the exploration of potential underlying mechanisms of treatment effects. Because this study is performed in collaboration with the principal investigator of the original study [4], we rely on learnings from that study rather than conducting a small-scale pre-study pilot and/or feasibility trial. The intervention will be based on the hypnosis scripts by Lindeløv et al. translated from Danish to Norwegian [4].

### Study setting and participants

Eligible participants are recruited at the department of cognitive rehabilitation at Sunnaas Rehabilitation Hospital ([name]). The department discharge approximately 370 patients a year making it realistic to reach the target sample size. Assessments and interventions will be conducted at the outpatient clinic at the Sunnaas Rehabilitation Hospital. The therapist will collect signed written informed consent forms before baseline assessments.

### Eligibility criteria (10)

#### Inclusion and exclusion criteria

Inclusion criteria are a documented nonprogressive ABI, minimum 12-month post-injury, ongoing WM deficits (by self-report and/or neuropsychological assessment), and age between 18 and 67 years. Exclusion criteria are severe mental illness (e.g., diagnosed major depressive disorder, schizophrenia, or bipolar disorder), progressive neurologic disease, and/or ongoing ICD-10 diagnosis of substance use disorder or lack of Norwegian language skills. Participants will be discouraged from participating in intensive in-patient cognitive rehabilitation while included in the trial but will not ask them to refrain from ordinary long-term community-based treatment such as physiotherapy and/or occupational therapy. Service provision during the trial will be documented.

### Included measures

Three sources of data will be collected: (1) demographic and medical data, (2) performance-based neuropsychological measures, and (3) subjective ratings of WM, emotional distress (anxiety and depression), quality of life, activity, and community integration (Fig. 1).

**Fig. 1 Fig1:**
[figure not shown]
Standard Protocol Items: Recommended for Intervention Trials (SPIRIT)

### Patient characteristics

Sociodemographic variables will include age, gender, marital status, children, living conditions, years of education, profession, and study or employment status. Medical variables include preexisting comorbidity, substance use, concurrent somatic and psychiatric diseases and injury characteristics of interest time since injury, etiology, and results of radiological examinations for lesion characterization.

### Interventions

The treatment protocol is identical to the study that is being replicated. During the first phase of the study, the treatment group and the active control group will receive identical procedures, including welcoming, hypnotic inductions, hypnotic re-alerting, and farewell. The groups differ in between the hypnotic induction and hypnotic re-alerting. The targeted procedure consists of suggestions about enhancing WM functions through the instantiation of preinjury WM ability in the present using age regression and visualizations of brain plasticity. The non-targeted suggestions contain no explicit mention of brain injury or WM-related abilities and thus serve as an active control, i.e., to isolate the ‘targetedness’ of suggestion as the independent variable by factoring out other influences from placebo, retest effects, etc. These non-targeted suggestions are borrowed from mindfulness meditation practices, involving body and thought awareness as they have demonstrated no or small effects on cognitive abilities in participants with ABI [48, 49]. All sessions will last for about 1 h, and the patients are invited to either sit in a comfortable chair or lay down on a bench during the procedures. We have access to the full treatment manual used by Lindeløv et al. in Danish. The manual has been translated into Norwegian. Throughout the spring of 2021, we tested the manual with the active treatment condition with two user representatives at Sunnaas Rehabilitation Hospital. This has given us the opportunity for closer collaboration with users regarding feasibility and adherence to intervention protocol.

To secure compliance to the protocol, regular supervision is provided to the therapist conducting the intervention. There are few side effects of hypnosis, and most people report well-being after hypnotic intervention. Participants are informed about the harmless nature of hypnosis, but also that if they wish to end the session for any reason, treatment will be immediately aborted. The therapist registers any occurrence of uncomfortableness or adverse effects of the treatment. Participants will further be informed that this is an experimental study with unknown effects. Participation is not time-consuming and will not be at the expense of other treatment.

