### Randomization and blinding

Eligible patients will be identified by the study PI (author [name]) from the department of cognitive rehabilitation (KReSS) at Sunnaas Rehabilitation Hospital. After baseline assessment, participants will be randomly allocated to either of the three groups. The randomization sequence will be generated electronically in STATA by an independent statistician.

The allocation sequence will be stored in a database that can only be accessed by the study’s principal investigator. It will not be possible to blind neither the participants nor the PhD candidate who will conduct the hypnotic suggestions. Outcome assessments will, however, be blinded in that a person external to the study will perform these without knowledge of group allocation. Our research group has extensive experience in managing blinded clinical trials, and we are confident that this can be conducted in a truly blinded way without contamination. Data analysis will also be blinded in that fake ID numbers will be assigned to participants in the final database, ensuring that the statistical analysis is performed without knowledge of true group content until after the analyses are finalized.

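### The only adverse-effect recording described is by the unblinded therapist and is tied to the treatment, so it gives no like-for-like record across the three arms or at T2 and T3

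*Protocol article*

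**What the plan says.** The Interventions section of the protocol article contains the one explicit statement on recording harms: "The therapist registers any occurrence of uncomfortableness or adverse effects of the treatment". The same paragraph says that side effects of hypnosis are few. It then describes what participants are told: "Participants are informed about the harmless nature of hypnosis", that they may end a session at any time, and that "this is an experimental study with unknown effects".

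On who knows the allocation, Randomization and blinding states: "It will not be possible to blind neither the participants nor the PhD candidate who will conduct the hypnotic suggestions". Outcome assessments are handled differently: "a person external to the study will perform these without knowledge of group allocation".

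The abstract describes the third arm as "a passive control group without intervention", and Trial design adds: "The passive control group will be assessed at the same time points as the other two groups to isolate retest effects". Those time points are baseline (T1), 5 weeks (T2) and 25 weeks (T3).

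**The concern.** A comparison of harms between randomized arms needs the same question, asked in the same way and at the same times in every arm. The described rule falls short in three respects. The recorder knows the allocation and delivers the treatment. The wording attaches adverse effects to the treatment, which has no counterpart in an arm that receives none. The recorder's described contact with participants after randomization is the four weekly sessions, whereas follow-up runs to week 25.

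The stake is practical. The Discussion says that, if the trial succeeds, the authors wish to provide recommendations and materials for using hypnotic suggestion after acquired brain injury. A reader of such a recommendation will want to know how often patients in each arm felt worse, and the described log cannot answer that for the passive arm. In addition, participants who have been told that a treatment is harmless might be less inclined to report a bad experience. That is a plausible mechanism, but nothing in the article allows its size to be judged.

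**Working it through.** The plan gives no figure for harms to reproduce. The check sets the statements side by side and adds simple arithmetic on the schedule.

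1. **Recorder.** Interventions names the therapist. Randomization and blinding says that the person conducting the hypnotic suggestions is not blinded. I take these to be the same role. The blinded external assessor is given outcome assessments, and no adverse-event task is described for that person.

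2. **Arms covered.** Both session arms meet the therapist four times. They share welcoming, induction, re-alerting and farewell, so the log can cover them on the same schedule. The passive arm meets the therapist at consent (Study setting and participants), but no later contact is described. That arm is 30 / 90 = 33% of the planned sample.

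3. **Time covered.** The sessions fall before T2. From T2 to T3 is 25 − 5 = 20 weeks, which is 20 / 25 = 80% of follow-up. No end date is set for the therapist's recording, but no contact is described through which it would continue.

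4. **Measurement schedule.** Included measures lists three sources of data: demographic and medical data, neuropsychological tests, and subjective ratings. Table 1 lists the instruments at T1, T2 and T3. Neither contains an adverse-event item, so the recording rule and the visit schedule do not meet.

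5. **Indirect sources.** These are present and have to be counted:
   - The Hopkins Symptom Checklist, QOLIBRI, the Patient Competency Rating Scale, PART-O and the cognitive tests are given in all arms at all three visits (Outcomes, Table 1). They can show average worsening in mood, quality of life, function or cognition. Statistical methods analyses continuous outcomes as means in mixed models, which can conceal deterioration in a few individuals.
   - Reasons for drop-out are recorded for leavers willing to give them (Dropout and data retention).
   - Service provision is documented (Inclusion and exclusion criteria), but use of services is not a record of symptoms.

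6. **Statements on safety.** One paragraph of Interventions says that side effects are few and also that participants are told hypnosis is harmless. Few is not none, so these two do not sit together. The statement that effects are unknown is less clearly in conflict, because it may refer to benefit.

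**The case against.** The strongest reply is that this is a condensed article. It does not say that nobody else records harms or that nothing is asked at T2 and T3. Detailed adverse-event procedures usually stand in the full protocol, and neither that document nor the SPIRIT schedule in Fig. 1 is available here. Table 1 is a list of outcome measures, so the lack of an adverse-event form in it proves little. This stands as a limit on the point: one can say what the article describes, not what the trial fails to do.

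A reader might go further and infer that the passive arm and the months after the last session yield no harm data at all. The documents do not support that. The scales in Table 1 reach every arm at both follow-up visits, and drop-out reasons and service use are recorded. Nor does it follow that harms cannot be compared between any arms, since the two session arms share a recorder and a schedule. The words on uncomfortableness are also broad, and no formal causality judgement is described.

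It may also be said that the harmless and unknown-effects statements contradict each other outright. They need not, if the unknown effects are benefits, and the actual consent wording is not shown. The tension between few side effects and harmless is the clearer one.

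What the reply leaves untouched is the rule that the article does state. It names an unblinded recorder and effects of a treatment that one arm does not receive. The indirect sources do not turn that into an adverse-event record comparable across the three arms.

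**Conclusion.** The point holds in a limited form. As described, adverse-effect recording rests with an unblinded therapist and is worded around the treatment. It therefore gives no comparable adverse-event record for one arm in three and no stated adverse-event enquiry at either follow-up visit. The indirect sources soften this but do not replace such a record.

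The conclusion assumes that the therapist and the person delivering the hypnotic suggestions are the same role, and that no fuller procedure exists in a document not shown. If one does, a sentence in the article would settle most of the point.

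A reader might also argue that 30 patients per arm are too few to show that hypnosis is harmless. That is beside the point. No stated objective is to demonstrate safety, and better recording would not change the sample size. The change is worth making because it is cheap and bears on the stated aim of implementation. It does not affect the validity of the efficacy comparison.

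**What to change.** Add one identical, self-completed adverse-experience item to the T2 and T3 questionnaires in all three arms, asking about new or worse symptoms since the last visit and their severity. Self-completion keeps the blinded assessor out of a conversation that could reveal the allocation. Keep the therapist's session log as a separate source and do not pool it with the questionnaire item. Tabulate events by arm regardless of whether anyone judges them related to treatment. If a fuller procedure already exists, state in the article that it applies alike to all arms and when.

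Reconcile the three statements in Interventions on few side effects, the harmless nature of hypnosis and unknown effects, so that the text and the participant information agree.

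The cost is one item at visits already scheduled and an ethics notification. Trial status puts the start of recruitment at October 2022 and its expected end at June/July 2024, so coverage will be partial. Participants already past T3 when the item is introduced will lack it altogether, and those between T2 and T3 will have it only at T3. The report should give the number asked in each arm as the denominator. If follow-up is already complete, the limitation should be stated with the results, alongside the therapist's log for the two session arms.
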